## Abstract

**Background:**

Proteinuria is a major marker of chronic kidney disease (CKD) progression and the predictor of cardiovascular mortality. The rapid development of renal failure is expected in those patients who have higher level of proteinuria however, some patients may have slow decline of renal function despite lower level of urinary protein excretion. The different mechanical (visco-elastic) and chemical properties, as well as the proteome profiles of urinary proteins might explain their tubular toxicity mechanism. Brillouin light scattering (BLS) and surface enhanced Raman scattering (SERS) spectroscopies are non-contact, laser optical-based techniques providing visco-elastic and chemical property information of probed human biofluids. We proposed to study and compare these properties of urinary proteins using BLS and SERS spectroscopies in nephrotic patient and validate hybrid BLS-SERS spectroscopy in diagnostic of urinary proteins as well as their profiling. The project ultimately aims for the development of an optical spectroscopic sensor for rapid, non-contact monitoring of urine samples from patients in clinical settings.

**Methods:**

BLS and SERS spectroscopies will be used for non-contact assessment of urinary proteins in proteinuric patients and healthy subjects and will be cross-validated by Liquid Chromatography-Mass Spectrometry (LC-MS). Participants will be followed-up during the 1 year and all adverse events such as exacerbation of proteinuria, progression of CKD, complications of nephrotic syndrome, disease relapse rate and inefficacy of treatment regimen will be registered referencing incident dates. Associations between urinary protein profiles (obtained from BLS and SERS as well as LC-MS) and adverse outcomes will be evaluated to identify most unfavored protein profiles.

**Discussion:**

This prospective study is focused on the development of non-contact hybrid BLS - SERS sensing tool and its clinical deployment for diagnosis and prognosis of proteinuria. We will identify the most important types of urine proteins based on their visco-elasticity, amino-acid profile and molecular weight responsible for the most severe cases of proteinuria and progressive renal function decline. We will aim for the developed hybrid BLS - SERS sensor, as a new diagnostic & prognostic tool, to be transferred to other biomedical applications.

**Trial registration:**

The trial has been approved by ClinicalTrials.gov (Trial registration ID NCT04311684). The date of registration was March 17, 2020.

## Background

Urine generally represents the fluid biopsy of the kidney, providing an alternative to blood plasma as a potential source of disease biomarkers [1, 2]. Therefore, discharged urine can serve as the human biofluid medium for noninvasive assessment of the kidney health status [3]. Healthy urine contains many end-product metabolites, electrolytes and few amounts of small proteins (selective proteins, that filtered from glomerular baseline membrane), that called albumin in normal range of up to 20–30 mg/dL. Any excessive range of albumin more than 30 mg/dL or appearance “big proteins” (non-selective proteins) called microalbuminuria or proteinuria [4].

Proteinuria is recognized as a major marker of chronic kidney disease (CKD) severity, the predictor of renal function decline and cardiovascular mortality [5–8]. The main pathway of progressive renal scarring is caused by tubular toxicity of filtering proteins, so more, the rapid development of end-stage kidney disease (ESKD) is expected in those patients who have higher level of proteinuria [9, 10]. However, despite high level of proteinuria, paradoxically, some patients may have slow decline of renal function compared to those patients with lower level of urinary protein excretion. This may possibly due to their different mechanical (viscosity, elasticity and compressibility) and chemical properties, as well as the different proteomic structure of the excreting urinary proteins [11]. Thus, there is a continuing uncertainty, why severity of renal failure progression could differ between proteinuric patients?

To date, different diagnostic methods in clinical settings can be used to ascertain urinary proteins. The extent of proteinuria can be gauged using an albumin-specific dipstick, immunochemical techniques, and high-performance liquid chromatography [12, 13]. However, results may vary between the methods, possibly due to different type, origin and size of excreting urinary proteins. The quality and quantity of filtered proteins, especially their mechanical properties such as physical viscosity [14, 15] compressibility [16] and chemical properties [17], such as amino-acid sequence (type of peptides), and molecular weight (low, middle and high molecular weight proteins), identify what kind of urinary proteins are more toxic and hazardous [1, 17]. Further studies including different areas of biomedicine and biophysics are needed to better understand importance of mechano-chemical characteristics of urinary proteins, in providing diagnostic and prognostic information that influences patient care and outcomes.

Measuring the viscosity, elasticity and chemistry of biological fluids is an important analytical tool in diagnostic, prognostic, and preventive medicine and research [14, 15]. The viscosity of biological solvents helps in gaining insight into the kinetics and dynamics of molecular and cellular processes such as conformational changes in protein [18, 19]. Such optical techniques as Brillouin and Raman spectroscopies to analyze human biofluids are very attractive for potential non-contact and fast clinical diagnostics with minimal or no sample preparation, without alteration of the fluid obtained from the body, representing a powerful simplification over most current techniques. Recently, dual Brillouin-Raman spectroscopy has been demonstrated as a viable diagnostic sensing tool in variety of biomedical applications [20–23].

The goal of the project is to develop and validate combined Brillouin & Surface-Enhanced Raman Scattering (SERS) Spectroscopy technique for simultaneous non-contact assessment of visco-elastic and chemical properties of human urine proteins as biomarkers of kidney disease. Systematic studies of these properties in proteins of urine samples to be taken from diseased and healthy subjects will be cross-validated by Liquid Chromatography Mass Spectrometry (LC-MS). The project ultimately aims for development of optical spectroscopic sensor for rapid, non-contact monitoring of urine samples from patients in clinical setting.

## Methods

### Study design

This project is prospective observational validation study, including subsequently the following three stages: measurement validation and protocol development (10–14 months), participant recruitment and evaluation (4–6 months), follow up and outcome assessment (10–14 months). Each stage consists of defined tasks, presented in Fig. 1.

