### Statistical analysis

All statistical analyses will be performed using STATA MP Version 15 (STATA Corporation, College Station, TX) statistical package. Two-sided *P-*values less than 0.05 will be reported as a significant for all analyses. Mean ± standard deviation (SD) for normal and median - interquartile range (IQR) for abnormal distribution of numerical variables will be shown in all data. Categorical variables will be presented as numbers (percentage). Categorical variables will be compared using Chi-square test or Fisher’s exact test and continuous variables will be compared using Kruskal–Wallis and/or Mann–Whitney U-test, as appropriate. Comparison of repeated two or more variables will be assessed with Wilcoxon and/or Friedman test as appropriate.

Obtained measurements of urinary protein by Brillouin and SERS/Raman spectroscopy will be compared with LC-MS data from same participant urine samples. Correlation between Brillouin and SERS/Raman spectroscopy parameters, LC-MS data and clinical-laboratory data of patients as well as healthy participants will be provided using Pearson’s or Spearman’s correlation as appropriate.

Univariate logistic regression will be used to test the association of several risk factors with high level of proteinuria. Multivariate logistic regression analysis will be used to assess the predictors for adverse outcomes. A receiver operator characteristics curve (ROC curve) analysis will be performed to identify the sensitivity, specificity, negative and positive predictive values of cut-off levels of Brillouin and SERS/Raman spectroscopy parameters in prediction of high proteinuria. Between measurement comparison of AUC will be provided with method developed by DeLong et al. [25].

During 1 year of follow-up, all adverse events such as exacerbation of proteinuria, progression of CKD, complications of nephrotic syndrome (thrombosis, nephrotic crisis, infection, including death), disease relapse rate and inefficacy of treatment regimen will be registered with referencing incident dates. Unadjusted and adjusted regression models will be evaluated to identify the association between urinary protein profiles defined by Brillouin and SERS/Raman spectroscopy and abovementioned adverse outcomes.

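### The follow-up stage may last only 10 months although 1 year of follow-up is promised, and the one model named for adverse outcomes uses neither time at risk nor the recorded event dates

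*Protocol article*

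**What the plan says.** The Study design section describes a project "including subsequently the following three stages": measurement validation and protocol development, then "participant recruitment and evaluation (4–6 months), follow up and outcome assessment (10–14 months". The recruitment stage thus comes before the follow-up stage, and the latter may be as short as 10 months.

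Two other places give a fixed length. The Methods part of the abstract states "Participants will be followed-up during the 1 year", and the Statistical analysis section begins its last paragraph with "During 1 year of follow-up, all adverse events such as exacerbation of proteinuria, progression of CKD". That paragraph adds that events, down to "disease relapse rate and inefficacy of treatment regimen will be registered with referencing incident dates", are dated.

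On analysis, the same section says "Multivariate logistic regression analysis will be used to assess the predictors for adverse outcomes". It later assigns the association between urinary protein profiles and the adverse outcomes to unadjusted and adjusted regression models whose type is not given. The Blood and urine samples section places the control renal function tests and ACR or PCR at the end of follow-up, without a month. The Outcome measures section makes the identification of hazardous protein profiles the secondary outcome.

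**The concern.** A follow-up stage of 10 months cannot give 1 year to a participant who enters at the end of recruitment. The plan therefore permits a schedule under which its own follow-up commitment fails for the later entrants.

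The second part concerns the analysis. With unequal observation time, a yes/no outcome in a logistic model treats a patient watched for 10 months and free of events as equal to one watched for 12. A patient lost early has to be coded one way or the other. The incident dates, which the study takes the trouble to record, are not used.

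What is at stake is the precision and clarity of the associations with adverse outcomes in a group of 80 patients. The primary outcome, the development and validation of the spectroscopy, does not depend on the length of follow-up.

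**Working it through.** The article gives no figure for the number of participants with complete follow-up, so there is nothing to reproduce. The check is calendar arithmetic plus an illustration of risk.

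**Inputs from the article**
- Recruitment length R: 4 to 6 months (Study design).
- Follow-up stage length F: 10 to 14 months (Study design).
- Stages in sequence (Study design).
- Stated follow-up: 12 months (abstract; Statistical analysis).
- Patients: 80 (Participants).
- Project length: 3 years (section on expected impacts).

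**Assumptions**
- Uniform accrual over R.
- Constant hazard, with a 12-month risk of 20%, 30% or 50%. The article gives no event rate.

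**Step 1. Available follow-up.** A participant enrolled at month t of recruitment has (R − t) + F months. The shortest is F (last enrolled) and the longest is R + F (first enrolled).

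**Step 2. Share with less than 12 months.** The share is max(0, 12 − F) / R.

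| F (months) | R = 4 | R = 5 | R = 6 |
|---|---|---|---|
| 10 | 2/4 = 50% (40 of 80) | 2/5 = 40% (32) | 2/6 = 33% (about 27) |
| 11 | 1/4 = 25% (20) | 1/5 = 20% (16) | 1/6 = 17% (about 13) |
| 12 or more | 0 | 0 | 0 |

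At F = 10 the affected participants have between 10 and 12 months. Mean follow-up, cut at 12 months, is 11.5 months for R = 4 and 11.67 months for R = 6.

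**Step 3. Effect on the risk.** The hazard is h = −ln(1 − p12)/12 and the risk at t months is 1 − exp(−h·t).

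| Assumed 12-month risk | 10-month risk | Odds ratio, 12 v 10 months | 16-month risk | Odds ratio, 16 v 10 months |
|---|---|---|---|---|
| 20% | 17.0% | 1.22 | 25.7% | 1.70 |
| 30% | 25.7% | 1.24 | 37.8% | 1.76 |
| 50% | 43.9% | 1.28 | 60.3% | 1.94 |

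The 12 v 10 column applies if events are counted up to 12 months, as the article states. It is the extreme case, because only the very last entrant has exactly 10 months. The 16-month columns apply only if follow-up ran instead to one common closing date. With F = 10 the first entrant then has at most 6 + 10 = 16 months.

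**Step 4. Room in the project.** The permitted schedules total 10 + 4 + 10 = 24 to 14 + 6 + 14 = 34 months. With a 12-month minimum for the last stage the shortest becomes 10 + 4 + 12 = 26 months and the longest stays at 34, inside 36.

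**The case against.** The best defence is that 10–14 months is a project-timeline estimate. It brackets 12, and the first stage carries the same range. If every participant does receive the stated year, follow-up is equal by design apart from death or loss, and a binary 1-year outcome in a logistic model is defensible. It also suits outcomes read only at the closing assessment, such as change in renal function. Model type and censoring rules may be set out in an analysis plan that is not shown.

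Much of this stands. The shortfall is conditional on a last stage of under 12 months, and it touches only those enrolled in the last 12 − F months. What the defence does not remove is that the stated range allows a duration the stated follow-up cannot fit. Nor does it remove that logistic regression is a stated choice for predictors of adverse outcomes, made alongside the recording of incident dates.

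A reader might infer more than the article supports:
- **Follow-up of 10 to 20 months in one study.** These belong to different schedules. Ten months needs F = 10, where the maximum is 16. Twenty months needs F = 14, where the minimum is 14. Within one schedule the spread is the recruitment length, 4 to 6 months, and nothing beyond 12 months counts if the stated year is applied.
- **One common closing date.** The Blood and urine samples section does not say this. The closing tests could equally fall at each participant's own year.
- **Secondary outcome analysed by logistic regression.** The profile-outcome associations are given to regression models of unnamed type, so a time-to-event model is not excluded.
- **Biased associations.** Bias would require enrolment date to be related to protein profile, and the article gives no such link. Otherwise the expected effect is some dilution.

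**Conclusion.** The concern holds as a conditional inconsistency of moderate severity. The lower bound of the follow-up stage, "follow up and outcome assessment (10–14 months", is shorter than the stated 1 year. At that bound about 33% to 50% of the 80 patients would have 10 to under 12 months, assuming uniform accrual. At 12 months or more nobody falls short.

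Counting events to 12 months, the distortion is modest: an odds ratio of about 1.2 to 1.3 between 12 and 10 months of observation, given a constant hazard and a 12-month risk of 20% to 50%. A common closing date would widen the contrast within one schedule to at most 10 against 16 months (26% against 38% at an assumed 30% risk), but the article does not state such a date.

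On the analysis, logistic regression is the only model named for predictors of adverse outcomes, and it ignores both time at risk and the recorded dates. It is not established that every outcome analysis is logistic, nor that the associations are biased. Only the secondary outcome is affected.

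**What to change.** 1. In Study design, state that the last stage runs at least 12 months after the last enrolment, for example 12–14 months.
2. In Blood and urine samples, tie the closing renal function tests and ACR or PCR to 12 months after each participant's enrolment.
3. In Statistical analysis, name a time-to-event model such as Cox regression for the dated adverse events, with censoring at 12 months or last contact. Keep logistic regression for outcomes read only at the 12-month assessment. Say which of these models serves the profile-outcome associations.

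The cost is up to 2 more months at the lower bound, with the longest schedule unchanged at 34 months in a 3-year project, and a little more analysis work. No extra patients are needed. Step 1 should be settled before recruitment closes, because follow-up time not observed by the end of the last stage cannot be recovered.

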**Fig. 1 Fig1:**
[figure not shown]
Flow diagram illustrating study design, tasks and procedures. SERS: surface enhanced Raman scattering, LC-MS: Liquid Chromatography-Mass Spectrometry, GFR: glomerular filtration rate

### Participants

The 80 patients with proteinuria will be recruited form National Scientific Medical Center, admitted to the internal medicine department. Age and gender matched 20 healthy volunteers will be enrolled from the outpatient clinics. The inclusion criteria are both male and female patients with any ethnic group, aged between 18 and 65 years old and newly diagnosed patients with glomerulonephritis and different range of proteinuria. The following exclusion criteria will be used: patients aged < 18 and > 65 years, glomerular filtration rate (GFR) < 60 ml/min, pregnant females, patients with diabetes mellitus, cancer, infectious diseases, and other life-treating comorbidities/conditions. Clinical and demographics data of the participants, medical history, comorbidities and data related to the disease will be recorded in case report forms.

### BLS spectroscopy

BLS spectroscopy (Fig. 2) will be performed using Torus single longitudinal mode 532 nm laser (Laser Quantum, England) in conjunction with high contrast scanning 6-pass tandem Fabry-Perot interferometer (TFPI) coupled with confocal microscope and imaging system (JRS Instruments, Switzerland) and separately by high speed Brillouin hyperfine spectrometer employing virtual image phase array (VIPA) (Light Machinery, Canada) to measure Brillouin spectra from human biofluids for assessment of their viscoelastic properties.

**Fig. 2 Fig2:**
[figure not shown]
Schematic demonstration of BLS Spectroscopy using scanning 6-pass TFPI coupled with confocal microscope. M: Mirror, F: Filter, L: Lens or Objective, IL: Imaging Lens, BS: Beam Splitter, CCD: Charge-Coupled Device, TFPI: tandem Fabry-Perot interferometer, PR: prism, PMT: photo-multiplying tube

### SERS/Raman spectroscopy

Raman spectroscopy (Fig. 3) will perform using Horiba LabRAM HR Raman microscope with 785 nm laser excitation and × 100 or × 10 microscope objectives. The SERS spectroscopy will be performed on urine samples stirred with commercial 60 nm diameter gold nanoparticles (742,015, from Sigma Aldrich, UK). Prior to mixing with urine samples, those nanoparticles would go through three centrifugation/ resuspension cycles in order to remove stabilizing agents/reagents from the nanoparticle suspension as described in publication of Gudun et al., [24]. After stirring with urine, taken from patients, suspension of gold nanoparticles will be dropcasted on some spots on commercial gold film coated slides (CA134 from Dynasil Corp., USA), they will get dried and multiple Raman spectra will be measured on those spots for each sample with above mentioned Raman microscope and those spectra will be averaged.

**Fig. 3 Fig3:**
[figure not shown]
Schematic demonstration of Raman Spectroscopy. M: Mirror, F: Filter, L: Lens or Objective, BS: Beam Splitter, DM: Dichroic Mirror, G: Grating, CCD: Charge-Coupled Device

### Hybrid Brillouin-SERS system

We propose to construct hybrid Brillouin-Raman system, which will simultaneously assess both visco-elastic (i.e. mechanical) and chemical properties at the same time from the same excitation laser source (532 nm or 780 nm). In this arrangement our Brillouin hyperfine spectrometer (Light Machinnery, Canada) system will be coupled with confocal microscope (Nicon, Japan) and Nanofinder Raman spectrometer (SOL Instruments, Belarus) and motorized sample stage (Standa, Lithuania) for 3D imaging The schematic of the proposed hybrid all-optical system is displayed in the Fig. 4.

**Fig. 4 Fig4:**
[figure not shown]
Schematic demonstration of hybrid BLS-Raman Micro-Spectroscopy sensing system. M: Mirror, F: Filter, L: Lens or Objective, CL: Cylindrical Lens, IL: Imaging Lens, BS: Beam Splitter, PBS: Polarizing Beam Splitter, DM: Dichroic Mirror, SMF: Single Mode Fiber, G: Grating, FPE: Fabry-Perot Etalon, CCD: Charge-Coupled Device, VIPA: virtual image phase array, QWT: quarter-wave plate

### Liquid chromatography-mass spectrometry

A reversed-phase LC-MS will perform for profiling of urine protein. LC-MS system consists of a Dionex HPLC pump (Ultimate 3000 RSLCnano System, Thermo Scientific) and UHR-QqTOF mass spectrometer Impact II (Bruker). Protein sample will be injected through trapping column setup Acclaim PepMap100 C18 5 mm × 300 um pre-column (Thermo Scientific) and peptides separated on an analytical Acclaim Pep-Map 15 cm x 75um RSLC column (Thermo Scientific) using 75 min multistep acetonitrile gradient (buffer A: 0.1% FA; buffer B 90%ACN/ 10% H2Oin 0.1% FA) at a flow rate of 0.3 ul/min. Data analysis will be performed through Mascot software using the SwissProt protein database. Furthermore, protein samples differentiated according to their molecular weights will be separately assessed by dual Raman-Brillouin hybrid system for comparative mechano-chemical characteristics and correlations.

### Blood and urine samples

Full blood biochemistry and corresponding urinalysis will provide additional information about participant health condition, such as functional condition of liver, kidney, heart, metabolic status etc. These widely evaluated routine laboratory data will be obtained from all participants. Routine blood metabolic profile including total protein, albumin, renal and liver function tests, coagulation tests, lipid profiles as well as urinalysis, proteinuria, albumin to creatinine ratio (ACR) and protein to creatinine ratio (PCR) will be performed at the study enrollment. Control renal function tests and ACR or PCR will be performed at the end of the follow up period. All blood and urine samples from participants will be collected at the time of hospital admission or at the visits to outpatient clinic. All blood and urine samples will be stored at -80co freezers for proper preservation before further visco-elastic and chemical analysis will be performed. After last patient is enrolled to the study, all laboratory evaluations will be provided according to the study protocol.

### Ethics statement

The project team is strongly committed to comply with the ethical policy. We guarantee that information provided in the frame of this project is reliable and unique. We confirm our adherence to research ethics, particularly preventing any fabrication and falsification of research data resulting in distorted research data, plagiarism and fake authorship. All work within the project will be conducted in accordance with international and national legal and ethical principles. All participants will follow ethical, health, safety and other relevant regulations. Laboratory research team and service contractors will be blinded from patients’ clinical data to assure clinically non-biased research. The knowledge acquired by this project will be completely disseminated via conventional academic channels such as international and national conference presentations and scientific publications. In order to defend intellectual property, the results of the project will be published in reputable peer-reviewed scientific journals of international standing.

